### Monitoring and evaluation

As per the Global AA-HA!,^16^ each city’s implementation plan will include process and outcome monitoring through data collected with the G-SHPPS and the GSHS. Progress in the implementation of interventions will be monitored by the team of local stakeholders and WHO on a periodic basis. For each agreed on activity/intervention in the implementation plan, monthly reporting will include whether the activity is not started, in planning, in progress or implemented, with a section for next steps and who is responsible.

Schools in the control arm will operate under ‘business as usual’ within their specific context, that is, they will not receive any intervention selected during the data-to-action workshop.

Follow-up G-SHPPS and GSHS surveys (the same as at baseline) will occur 2 years after the baseline surveys in all selected schools. For the GSHS, new classes from these schools will be randomly selected to ensure participation of 13–17 years old students similar in age to the baseline sample.

### Data management and analysis plan

During electronic data collection through Dataform (LimeSurvey),^33^ G-SHPPS data are uploaded to a secure server that will only be accessible by the city and WHO. Summary results of key indicators will be produced for each city.

GSHS data are collected on computer scannable answer sheets with no personal identifying information. Data will be processed using standard cleaning and generic data analysis programmes. A city-specific database will be generated and results will be displayed on a standard fact sheet including information on response rates, a summary of methods and weighted prevalence estimates with CIs.^15^

The Axivity AX3 data will be downloaded on-site and uploaded to a secure WHO server with unique identifiers, with no personal information. The unique identifier will be used to link these data to the student’s GSHS physical activity data. Time spent in total physical activity, moderate-to-vigorous-intensity physical activity, and in sedentary behaviour will be computed from the Axivity AX3 data for each student, using standard methods.^34 35^ Agreement between the Axivity AX3 and the questionnaire data will be assessed using approaches consistent with previous studies.^31 36^

For GSHS and G-SHPPS follow-up surveys, the same data analysis procedures as at baseline will be used.

To assess effectiveness of the interventions, comparative analysis of changes of policies and programmes and of students’ health behaviours between the intervention and control group will be undertaken. With most outcome variables being binary, most intervention effects will be estimated through adjusted ORs with 95% CIs, using random effects logistic regression to adjust for within-school clustering. Additionally, a score across multiple risk and protective behaviours will be computed for each city (depending on the selection of questionnaire modules in each city), and effectiveness of the intervention will also be tested using this score.^37^ Data analysts will be blinded to allocation of schools in the two arms.

The analysis will account for potential spillover effects as much as possible. Spillover effects are defined as benefits provided by interventions that extend beyond direct recipients and impact people in close physical or social proximity who did not directly receive the intervention themselves, namely students in the control arm.^38^

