### Study population and sampling

This study’s target population is 13–17 years old students. In each city, following standard G-SHPPS and GSHS sampling procedures,^14 15^ approximately 30 schools will be randomly selected from a list of schools including every school in the city with eligible classes (classes that the target population usually attends), provided by education authorities from the respective cities. Selection will be done by experts from WHO with probability proportional to the number of students in the eligible schools.

For the GSHS, in a second sampling stage, classes will be randomly selected from all eligible classes. All students of selected classes will be asked to participate in the survey.

The city sample size was calculated to test the hypothesis that the prevalence of behavioural risk factors would be lower among students in the schools of the intervention group versus those in the control group at follow-up using G*Power V.3.1.^26^ With most outcome variables (prevalence of behavioural risk and protective factors) being binary, logistic regression was selected as the statistical test, the required power level was set at 80% and the significance level prespecified at α=0.05. The to-be-detected effect was specified at an OR=0.75, which represents the average of pooled effect sizes from a recent meta-analysis^11^ considering universal school interventions across a range of behaviours, similar to the ones assessed in our study.

The initial sample size calculation resulted in n=473, which was inflated assuming a design effect of 1.5 and an expected response rate of 90%: 473×1.5/0.9=788. Finally, this sample size was quadrupled aiming at reporting for two age groups within both the intervention and control arm: 13–15 and 16–17 years, resulting in a target sample size of n=3153.

Participation in the G-SHPPS and GSHS is voluntary. For the GSHS, in line with local policies, consent will be obtained from the students themselves and/or their parents/guardians (see online supplemental appendix for consent forms).

10.1136/bmjopen-2022-071353.supp1Supplementary data

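### The follow-up rule repeats the baseline weighted city prevalence with no exception for arm, so read literally it gives treated schools the weight of untreated, unsampled ones

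*Protocol article*

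**What the plan says.** All quotations are from the Protocol article.

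- **Sampling** (Study population and sampling). The school frame is the whole city: "approximately 30 schools will be randomly selected from a list of schools including every school in the city with eligible classes". Schools are drawn "with probability proportional to the number of students in the eligible schools". They are then randomised to two arms (Study design and locations); the ratio is not given.
- **Baseline output** (Data management and analysis plan). "A city-specific database will be generated and results will be displayed on a standard fact sheet", and the sheet carries "a summary of methods and weighted prevalence estimates with CIs". How the weights are built is not described.
- **Follow-up coverage** (Monitoring and evaluation). "Follow-up G-SHPPS and GSHS surveys (the same as at baseline) will occur 2 years after the baseline surveys in all selected schools". Control schools receive none of the workshop interventions.
- **Follow-up output** (Data management and analysis plan). "For GSHS and G-SHPPS follow-up surveys, the same data analysis procedures as at baseline will be used".
- **Effectiveness.** The paragraph after that sets out a separate comparison of arms by random effects logistic regression.
- **Reporting by arm.** The sample size text quadruples the sample so that two age groups can be reported within each arm.

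**The concern.** At baseline the procedure is sound. No school has been treated, and a sample drawn with probability proportional to size from the full city list can be weighted to the city's students. Under that design each sampled school stands for roughly the same share of those students.

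At follow-up this breaks down. An intervention school with an unchanged weight speaks for unsampled schools that had no intervention. With equal arms, intervention schools carry about half the total weight however small a share of the city was treated. The pooled figure then tends to the average of the two arms, and a baseline-to-follow-up city change computed from it would absorb part of the trial's own effect. The more the intervention moves an indicator, the larger the error.

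The study's overarching aim includes generating health information for students of these cities, and GSHS results are to be shared with students, parents, teachers and communities. A reader would naturally take a follow-up fact sheet in the baseline format as a statement about the city.

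**Working it through.** **1. The plan's own figure.** 473 × 1.5 / 0.9 = 788.3, and 4 × 788.3 = 3153, so the stated city target reproduces. At 90% response, responders number 473 × 1.5 × 4 = 2838.

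**2. Inputs.**
- From the sample size text: odds ratio 0.75, design effect 1.5, 2838 responders per city.
- Assumed: equal arms, half the total weight in each arm, no spillover, and a control prevalence pC (20% as the main example).
- Not given, so shown as a range: f, the share of the city's eligible students in intervention schools. With equal arms, all sampled schools together hold about 2f.

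**3. Formulas.**
- pI = 0.75·o / (1 + 0.75·o), with o = pC / (1 − pC)
- Pooled figure = (pC + pI) / 2
- Actual city prevalence = pC + f(pI − pC)
- Error = pooled − actual = (0.5 − f)(pI − pC)
- SE of the pooled figure = √[p(1 − p) × 1.5 / 2838], with p the pooled figure

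**4. At pC = 20%.** o = 0.25, so pI = 0.1875 / 1.1875 = 15.8%. The difference pI − pC is −4.21 points and the pooled figure is 17.9%. SE = √(0.179 × 0.821 × 1.5 / 2838) = 0.88 points, so the half-width is 1.96 × 0.88 = 1.7 points. Coverage is the normal probability that the pooled 95% CI contains the actual city value.

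| f | Actual city % | Error (points) | Coverage of 95% CI |
|---|---|---|---|
| 0.05 | 19.8 | 0.45 × −4.21 = −1.9 | 42% |
| 0.10 | 19.6 | 0.40 × −4.21 = −1.7 | 52% |
| 0.25 | 18.9 | 0.25 × −4.21 = −1.1 | 78% |
| 0.50 | 17.9 | 0 | 95% |

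**5. Other prevalences, at f = 0.05.** The error is −1.0 points at pC = 10%, −2.6 at 30% and −3.2 at 50%. The half-widths are 1.3, 2.0 and 2.3 points.

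**6. Would control schools alone repair the city figure?** They estimate pC, so against the actual city value their error is −f(pI − pC). At pC = 20% this is +0.2 points at f = 0.05 and +0.4 at 0.10. At f = 0.25 it is +1.05, the same size as the pooled error of −1.05 and with a larger SE.

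**7. Weighting to the true treated share.** The estimate f·pI + (1 − f)·pC has no error of this kind. With 1419 responders per arm, its SE at pC = 20% is √[f²·pI(1 − pI)·1.5/1419 + (1 − f)²·pC(1 − pC)·1.5/1419]. This gives 1.24, 1.18 and 1.02 points at f = 0.05, 0.10 and 0.25, which is 1.4, 1.3 and 1.2 times the pooled SE.

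**The case against.** The strongest reply is that the article never says the follow-up fact sheet merges the arms. Cleaning, database generation and weighted estimation can all be run within arm, and the sample was enlarged so that results could be reported within arm. This stands as a limit: pooling is the literal reading of the sentence, not a declared intention. It does not remove the point. The sample size text explains a number, whereas the follow-up sentence sets a procedure, and the procedure it carries over is a single city-level one. The article is also a condensed document, but the concern is with a rule it states, not a detail it leaves out.

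Four stronger readings are tempting, and the document does not support them.

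- **The trial result is biased.** It is not. The effect analysis compares arms separately and does not use the pooled figure.
- **The follow-up figure must describe a half-treated city that does not exist.** That depends on f and on the allocation ratio, and neither is given. If the sample is nearly every eligible school and arms are equal, the half-treated city is real and the error vanishes.
- **School policy percentages from the G-SHPPS are wrong for the city.** The first objective covers policies in the selected schools, and no weighting is mentioned for that survey. A summary over those schools describes them correctly, so there is no stated city-wide target to miss. Mixing arms only makes it less informative.
- **The second objective, on levels in the cities, is misanswered at follow-up.** That objective is not tied to follow-up, and the baseline survey can answer it. No baseline-to-follow-up city trend is promised.

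Nor does the odds ratio of 0.75 apply to every indicator. Each city prioritises certain topics, and indicators the intervention does not move carry no such error.

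**Conclusion.** The concern holds as a defect in one stated rule for a descriptive output. Followed literally, the pooled follow-up GSHS city prevalence is off by (0.5 − f)(pI − pC) for indicators the intervention changes. At 20% control prevalence that is −1.9 to −1.1 points for f from 0.05 to 0.25, comparable to the 1.7-point half-width over much of that range, and it falls to zero at f = 0.5. The size rests on equal allocation, roughly equal total weight per arm, an effect at the planned odds ratio and no spillover. Any city-level change from baseline computed the same way inherits the error. The sentence should be changed, but the effectiveness conclusions do not depend on it.

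**What to change.** Replace the follow-up sentence with a rule in three parts:

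1. Follow-up weighted GSHS prevalence is reported separately by arm, using coded arms while analysts are blinded. G-SHPPS summaries are likewise shown by arm.
2. Any single city-level GSHS figure at follow-up uses weights in which intervention schools represent only themselves and control schools represent the rest of the city's eligible schools. The student counts used to draw the schools should supply the treated share f.
3. A figure from control schools alone is labelled as the level without the intervention, subject to the spillover the analysis section already anticipates. It is not presented as the actual city prevalence.

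The cost is a changed weighting step and a wider CI for the follow-up city figure, up to about 1.4 times when f is small. No new data are needed.

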**Methods and analysis:**

We will conduct a cluster randomised controlled trial in schools in Fez, Morocco; Jaipur, India; Saint Catherine Parish, Jamaica; and Sekondi-Takoradi, Ghana. In each city, approximately 30 schools will be randomly selected and assigned to the control or intervention arm. Baseline data collection includes three components. First, a Global School Health Policies and Practices Survey (G-SHPPS) to be completed by principals of all selected schools. Second, a Global School-based Student Health Survey (GSHS) to be administered to a target sample of n=3153 13–17 years old students of randomly selected classes of these schools, including questions on alcohol, tobacco and drug use, diet, hygiene, mental health, physical activity, protective factors, sexual behaviours, violence and injury. Third, a study validating the GSHS physical activity questions against wrist-worn accelerometry in one randomly selected class in each control school (n approximately 300 students per city). Intervention schools will develop a suite of interventions using a participatory approach driven by students and involving parents/guardians, teachers and community stakeholders. Interventions will aim to change existing structures and policies at schools to positively influence students’ behaviour, using the collected data and guided by the framework for *Making Every School a Health Promoting School*. Outcomes will be assessed for differential change after a 2-year follow-up.

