## Methods and analysis

### Study design and locations

We will conduct a multisite two-armed cluster randomised controlled trial using a nested cross-sectional design. The clusters are defined as schools and classes within schools. The study locations are spread across four world regions and include the cities of Fez, Morocco; Jaipur, India; Saint Catherine Parish, Jamaica; and Sekondi-Takoradi, Ghana. These locations (secondary cities) were purposefully selected in collaboration with WHO regional focal points to generate information for settings that are less likely to be in the focus or receive resources for adolescent health interventions.

In each city, approximately 30 schools will be selected and randomly assigned to either the intervention or control group. At baseline, all sampled schools will conduct a G-SHPPS to assess school policies and practices^14^ and a GSHS to assess risk behaviours and protective factors among students.^15^ Additionally, in the control group of each city, we will conduct studies to validate GSHS physical activity questions against an accelerometer (Axivity AX3^25^) to be worn by students on the wrist for 8 days prior to the baseline survey.

Following the baseline surveys, the intervention schools will participate in data-to-action workshops to develop a package of interventions. Students, parents, teachers, local authorities and researchers will work together to find and prioritise policy and programme solutions to establish a unified action plan. Subsequently, these interventions will be implemented, and study processes and outcomes will be assessed for differential change via repeat G-SHPPS and GSHS surveys after a 2-year follow-up. At follow-up, new classes will be selected from the same schools to ensure participation of 13–17 years old students similar in age to the baseline sample. We hypothesise that the prevalence of behavioural risk factors would be lower and the prevalence of protective factors higher among students in schools in the intervention group compared with the control group at follow-up. An overview of our study design is shown in figure 1.

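### The hypothesis and sample size concern prevalence at follow-up, but student outcomes are to be assessed as differential change; with new students at each wave, a follow-up comparison adjusted for school baseline is more precise

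*Protocol article*

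**What the plan says.** The article gives two targets for the student survey (GSHS) outcomes.

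- **Prevalence at follow-up.** Study design and locations hypothesises less risk behaviour and more protective factors in intervention schools "compared with the control group at follow-up". Study population and sampling sizes each city for the hypothesis that risk-factor prevalence "would be lower among students in the schools of the intervention group versus those in the control group at follow-up".
- **Change.** The abstract says: "Outcomes will be assessed for differential change after a 2-year follow-up". Study design and locations, which also holds the follow-up hypothesis, says that "outcomes will be assessed for differential change via repeat G-SHPPS and GSHS surveys after a 2-year follow-up". Data management and analysis plan announces "comparative analysis of changes of policies and programmes". Those words concern school policies, but the sentence goes on to students' health behaviours and compares the arms on both.

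The design is a "multisite two-armed cluster randomised controlled trial using a nested cross-sectional design", and "At follow-up, new classes will be selected from the same schools". The only model named is a random-effects logistic regression giving adjusted odds ratios. Within-school clustering is the only adjustment mentioned. Neither a school baseline prevalence nor an arm-by-wave term appears.

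**The concern.** A difference at follow-up and a difference in change are separate contrasts with separate variances. The sample size has no factor for a change contrast.

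In a cohort, subtracting baseline can pay for itself through the correlation within each student. Here different students answer at each wave, so only the persistence of a school's own level links the two surveys. Subtracting the baseline brings in the whole sampling error of the baseline survey. Schools are randomised, so differencing is not needed for validity. The precision would be given up for nothing in return.

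Leaving both contrasts in the text also allows the choice between them to be made after results are seen, over many outcomes and four cities.

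**Working it through.** **The plan's own figure.** 473 × 1.5 / 0.9 = 788.3, and × 4 = 3153.3, which matches the stated 3153. The steps are the initial n, the design effect, the response rate and the fourfold increase for age-group reporting by arm. None of them concerns change or a baseline correlation.

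**Inputs from the article.** Target 3153 per city, response 90%, about 30 schools, design effect 1.5.

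**Assumptions, not in the article.** The baseline and follow-up surveys are of equal size. Schools are split about 15:15. The design effect of 1.5 is due to school clustering alone. The cluster autocorrelation (CAC, the share of between-school variance that persists over two years) lies between 0.5 and 1.0.

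**Step 1: correlation of school prevalences across waves.**
- Respondents per school: m = 3153 × 0.9 / 30 = 94.6.
- ICC = (1.5 − 1) / (94.6 − 1) = 0.0053.
- r = m × ICC × CAC / (1 + (m − 1) × ICC). With CAC = 1, r = 0.505 / 1.5 = 0.337.

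This ceiling hardly depends on m. For one age group (m = 47.3, ICC = 0.0108) it is 0.341. If part of the 1.5 comes from classes, which are newly drawn at follow-up, r is lower.

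**Step 2: variance relative to an unadjusted follow-up comparison (= 1).**
- Unconstrained change: 2(1 − r).
- Follow-up adjusted for school baseline: 1 − r².
- Ratio of the two: 2(1 − r) / [(1 − r)(1 + r)] = 2/(1 + r), above 1 for every r below 1.

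**Step 3: cost of estimating the slope.** With about 30 schools, the adjusted variance is inflated by about 1 + 1/26 = 1.038.

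| CAC | r | Change | Adjusted | Change / adjusted | Same, after slope cost |
|---|---|---|---|---|---|
| 1.0 | 0.337 | 1.33 | 0.89 | 1.50 | 1.44 |
| 0.8 | 0.270 | 1.46 | 0.93 | 1.58 | 1.52 |
| 0.6 | 0.202 | 1.60 | 0.96 | 1.66 | 1.60 |
| 0.5 | 0.168 | 1.66 | 0.97 | 1.71 | 1.65 |

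**Step 4: adjusted against follow-up only, after slope cost.** At CAC 1.0, 0.887 × 1.038 = 0.92. At CAC 0.5, 0.972 × 1.038 = 1.01. The gain of 11% at most shrinks to about 8%, and to nothing at low r.

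**Step 5: larger ICCs (assumed, m = 94.6, before slope cost).** 2(1 − r) falls below 1 once r exceeds 0.5.

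| ICC | CAC | r | Change | Adjusted | Change / adjusted |
|---|---|---|---|---|---|
| 0.02 | 0.8 | 0.527 | 0.95 | 0.72 | 1.31 |
| 0.05 | 0.8 | 0.666 | 0.67 | 0.56 | 1.20 |

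Here change beats an unadjusted follow-up comparison but is still less precise than the adjusted one.

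These are linear approximations on school-level prevalences, not exact results for the logistic model.

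**The case against.** **The article never names unconstrained difference-in-differences.** This is the strongest reply. Its adjusted odds ratios list no covariates, a condensed article normally leaves model terms to the analysis plan, and differential change could loosely describe a two-wave model with the arms held equal at baseline. This stands in part: the ratios above are the penalty for one natural reading, not for a model the article has fixed. It does not remove the mismatch, because the article itself gives two contrasts for the same outcomes.

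**The policies half of the sentence is different.** The school policy survey returns to the same schools, so the new-students argument does not reach it. This stands, and the point is confined to the GSHS student outcomes.

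**A reader might infer that power falls below the planned 80%.** The documents do not support that. The 80% belongs to n = 473 (788 after inflation), while the target is four times 788. Taking 473 at face value with two-sided α = 0.05, a change variance of 1.66 on the full city sample gives 2.802 × √4 / √1.66 − 1.96 = 2.39, a power above 99%. The article does not state the base rate behind 473, so I attach no power figure to the change contrast in either direction.

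**A reader might infer that change is always worse than follow-up only, or that adjustment never loses.** Neither holds. The first needs r below 0.5. The second fails slightly at low r with about 30 schools.

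**Conclusion.** The mismatch is in the text: the hypothesis and sample size concern follow-up prevalence, while the abstract, design and analysis sections concern change. No bias follows from it. The cost is precision, together with an open choice of contrast.

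If change is analysed without constraint, its variance is about 1.5 to 1.7 times that of the baseline-adjusted follow-up comparison at the plan's design effect of 1.5, or about 1.4 to 1.65 times after paying for the slope. That rests on r of at most about 0.34, on an assumed CAC of 0.5 to 1.0 and on equal survey sizes. At assumed ICCs of 0.02 and 0.05 with CAC 0.8, the ratio is 1.3 and 1.2 before slope cost, still in favour of adjustment.

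Against an unadjusted follow-up analysis, change has about 1.3 to 1.7 times the variance at design effect 1.5, but can be the more precise of the two when schools differ more and are stable. Adjustment itself gains little over follow-up only. The main benefit is avoiding the differencing penalty and fixing one contrast.

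**What to change.** For the GSHS student outcomes, make the primary estimate the intervention-versus-control odds ratio at follow-up, from the random-effects logistic model already planned, adjusted for the school's baseline prevalence of the same outcome. A two-wave model with the arms constrained equal at baseline would serve the same purpose. Report unconstrained difference-in-differences only as a sensitivity analysis. Align the abstract, Study design and locations, Study population and sampling, and Data management and analysis plan to this one contrast, and describe the school-policy comparison separately.

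The cost is wording and one school-level degree of freedom per city, of about 28. No new data are needed: Trial status reports baseline collection finished in all four cities, so the school baseline prevalences can be computed from data in hand.

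### If change between arms is estimated from both waves with a school random intercept alone, class and school-by-wave variance is left out of the standard error and the 95% CIs are too narrow

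*Protocol article*

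**What the plan says.** Three statements in the protocol article bear on this point.

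- **Clusters.** Study design and locations: "The clusters are defined as schools and classes within schools". The same section gives the design: "We will conduct a multisite two-armed cluster randomised controlled trial using a nested cross-sectional design".
- **Follow-up sample.** Monitoring and evaluation: for the student survey (GSHS), "new classes from these schools will be randomly selected". The schools stay the same and the classes do not.
- **Effect model.** Data management and analysis plan: effectiveness rests on "comparative analysis of changes of policies and programmes", and of students' health behaviours, between the arms. Most effects are to be adjusted ORs with 95% CIs, "using random effects logistic regression to adjust for within-school clustering".

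The contrast is not stated in one way. The Abstract, the design section and the analysis section speak of change. The hypothesis in the design section is a difference "among students in schools in the intervention group compared with the control group at follow-up", and the sample size section powers the same follow-up comparison.

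**The concern.** The analysis section names an adjustment at school level, although the design declares two levels and renews the lower one at each wave. For a contrast of change this matters. A school intercept is shared by both waves, so it essentially cancels from the arm-by-wave term. What does not cancel is whatever differs between waves within a school: the particular classes drawn, and any movement of that school over two years. A model with only the school intercept has no term for either and counts them as independent student-level variation.

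The stake is the validity of the CIs for the binary GSHS indicators analysed this way. Intervals that are too short lead to claims of effectiveness that the data do not support.

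**Working it through.** **Inputs from the article.** About 30 schools per city; target n = 3153 per city; response rate 90%; design effect 1.5; α = 0.05; about 300 students in the validation study, from one class per control school.

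**Assumed.** About 15 schools per arm (the allocation ratio is not stated); a two-sided test; the split of clustering between school, school-by-wave and class; the outcome prevalence.

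**The plan's own figure.** 473 × 1.5 / 0.9 = 788.3, and 788.3 × 4 = 3153.3, so the stated chain from 473 to 3153 reproduces. 473 itself cannot be checked here, because no prevalence is given, and it does not bear on this point.

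**Cluster sizes.** 3153 / 30 = 105.1 students per school, of whom 105.1 × 0.9 = 94.6 respond. Class size is about 300 / 15 = 20.

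**ICC implied by the design effect of 1.5.** At school level, 0.5 / 93.6 = 0.0053. If it lies wholly at class level, 0.5 / 19 = 0.026.

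**Formula.** Let D = 1 + (m − 1) × ICC, where the ICC covers only the wave-specific part and m is the size of the unit that carries it. The true variance of the change contrast is D times what the school-intercept model reports. Hence type I error = 2 × [1 − Φ(1.96/√D)].

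| Wave-specific part | D | Model SE / true SE | Type I error |
|---|---|---|---|
| None | 1.00 | 1.00 | 5.0% |
| Half of the excess in 1.5 | 1.25 | 0.894 | 8.0% |
| All of the excess in 1.5 | 1.50 | 0.816 | 11.0% |
| Beyond the plan's figure | 2.00 | 0.707 | 16.6% |

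Exact doubling to 10% needs D = 1.42. That is a class ICC of 0.022 at 20 per class, or a school-by-wave ICC of 0.0045 at 95 per school.

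**Check by simulation.** No true effect, 30 schools (15 per arm), prevalence 30% (assumed), five classes of 20 per school per wave, 1,500 runs per row. The Wald test of arm by wave from a logistic model with a school random intercept only is set against a t test on school-level changes (28 df) and a follow-up-only model with a school intercept.

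| ICC: school / school-by-wave / class | Change, school intercept only | School-level change, t test | Follow-up only |
|---|---|---|---|
| 0.01 / 0 / 0 | 5.5% | 4.7% | 7.3% |
| 0.01 / 0 / 0.01 | 7.8% | 5.7% | 7.6% |
| 0.01 / 0 / 0.026 | 10.5% | 6.2% | 7.3% |
| 0.01 / 0 / 0.05 | 15.2% | 5.8% | 7.5% |
| 0.005 / 0.005 / 0 | 9.7% | 5.0% | 5.7% |
| 0.01 / 0.01 / 0.02 | 19.9% | 5.9% | 6.3% |

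In the third row the estimates have an empirical SD of 0.140, while the model reports an SE of 0.113. The ratio 0.113 / 0.140 = 0.81 agrees with the 0.816 from the formula. A separate simulation at 20% prevalence, with 95 students per school per wave, gave 5.1% with no wave-specific clustering and 11.9% with the whole design effect of 1.5 wave-specific.

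The last row assumes more clustering than the plan does: its wave-specific part alone is D = 1 + 99 × 0.01 + 19 × 0.02 = 2.37.

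**The case against.** The strongest reply is that the article never says the school is the only random term. It is a condensed account, does not write out the model, and may leave the random-effects structure to an analysis plan not shown. Within-school clustering can even be read to include classes. This stands in part, and it is why the point is conditional. It does not dispose of the matter. The article does state an adjustment, a contrast and a sampling scheme, and on the plain reading of the three together the standard error is too small.

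The second reply is that the hypothesis and the sample size concern the difference at follow-up. This also stands. With one wave, class variance is absorbed into the school effect. The follow-up-only column stays between 5.7% and 7.6% and does not rise with the class ICC. The small excess over 5% fits a Wald z test with 30 clusters. That simulation did not adjust for baseline, but the reasoning is the same when it does. The analysis section, however, is where the comparison is specified, and it compares changes.

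A reader might infer three stronger claims that the article does not support:

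- **That type I error roughly doubles.** This needs nearly all of the design effect of 1.5 to be wave-specific. The article does not say how that figure divides.
- **That every indicator in every city is affected.** Indicators with little wave-specific variance are not. The model is stated for most effects, not all. The school policy survey (G-SHPPS) has one response per school and so no class clustering.
- **That Wald intervals are too short for the change contrast merely because schools are few.** With no wave-specific variance the Wald test rejects 5.1% and 5.5% in the two simulations, so no such excess is shown.

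**Conclusion.** The point holds conditionally. If change is estimated from both waves with a school random intercept alone, the arm-by-wave standard error omits class and school-by-wave variance, and the 95% CIs are too narrow wherever that variance exists. On the plan's own design effect, coverage would fall to about 92% if half of the excess is wave-specific (type I error 8%) and to about 89% if all of it is (11%). The upper figure of about 20% rests on ICCs above what the plan assumes, and with no wave-specific variance there is no loss. These figures also rest on about 15 schools per arm, and the class-level ones on about 20 students per class. The direction of the error is certain under the stated condition; its size is not, because the article gives no ICC or between-wave correlation.

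**What to change.** First, settle the contrast, so that the hypothesis, the sample size section and the analysis section name the same one.

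- **If it is change:** add random effects for school-by-wave and for class within school-by-wave, alongside school. A class term alone would still leave out school-level drift. Alternatively, analyse one change per school, with school-level degrees of freedom (30 − 2 = 28 per city, assuming about 15 schools per arm) or a permutation test over schools. The school-level t test held 4.7% to 6.2% in the scenarios shown.
- **If it is the follow-up difference adjusted for baseline:** a school random effect with small-sample degrees of freedom is enough.

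The cost is a few sentences in the analysis plan and wider intervals: by √1.25 = 1.12 or √1.5 = 1.22 in the two cases based on the plan's design effect, and not at all where wave-specific variance is nil. That width is uncertainty the narrower intervals would have hidden. No change to sampling or data collection is needed, provided that each student record carries its school, class and wave.
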